**Fig. 1 Fig1:**
[figure not shown]
The “*Visitentool*” (german for “ward-round tool”). Inter-professional collaboration via an electronical communication platform. Nursing and physician staff as well as social services daily assess the clinical and functional situation about possible discharge (using simple, intuitive color coding) and propose possible discharge dates. Also, reasons for delays in discharge are being monitored

#### Module 2 Interprofessional collaboration, integral hospital and post-acute patient transition

Transparent and systematic interprofessional communication will reveal factors for delay in these polymorbid patients (pending diagnostics, medical treatments, administrative and organizational elements) throughout the hospital stay. Doing so, we will identify regional and socioeconomic (e.g., health care insurance status) differences in the patient care continuum. We hypothesize that longitudinal observation of patient transition will further allow measurement of effective time from initial request to a post-acute care institution to effective transfer with corresponding internal and external delaying factors (Fig. 2). We will systematically examine patient satisfaction, hypothesizing that it will not decrease upon the study intervention. Implementing a reengineered discharge questionnaire including the teach-back methodology, we aim to improve patient education [19, 20]. This effort will not only strengthen interprofessional coordination and communication, but also increase health care continuity across all hospital transition steps. Moreover, we systematically investigate reasons for low satisfaction.

**Fig. 2 Fig2:**
[figure not shown]
The “In-HospiTOOL”. An integrative patient management tool. The “In-HospiTOOL” has three components involving admission (inter-professional initial assessment, *“Ersterfassung”*), medical ward (inter-professional daily re-assessment, *“Visitentool”*), and discharge (inter-professional patient education, reengineered discharge [32]). PACD, Post-Acute Care Discharge [15, 18]

#### Module 3 benchmarking to advice health care authorities and stakeholders

The buildup of a large dataset including comprehensive patient information (demographics, clinical, organizational, health insurance status) will be a basis for future data sharing in Switzerland [21]. We hypothesize that this dataset from several hospitals will allow to identify associations of management factors and outcome data, thereby facilitating a better understanding how interventions affect patient outcomes. Convocation of a multi-professional sounding board with tailored implementation interventions [22] will be inevitable to built-up a data warehouse and thus, broad dissemination of our results with potential to improve health care service also in non-participating health care institutions.

### Endpoints

All patients will be daily assessed during hospitalization and contacted 30 days after admission by phone for a structured and blinded interview to assess primary and secondary endpoints.

The primary endpoint of this study is length of hospital stay within 30 days after admission including readmissions during this period (corresponding to Module 1). Length of hospital stay will be verified based on hospital data for the index hospital stay and complemented by 30-day interviews regarding possible secondary hospitalizations.

Secondary endpoints (corresponding to Module 1–3) include measures of patient-oriented outcomes:in-hospital and all-cause 30-day mortalityunplanned readmissions or unplanned general practitioner / ED visitsdelaying factors of ED- and medical ward’s floweffective time to hospital discharge after involving external institutions (time from transfer application to transfer)institutionalizationsatisfaction with ED-, ward-, and discharge processfunctional status (incl. Quality of life) using the EuroQol Group 5-Dimension Self-Report Questionnaire (see Additional file 1) [23].

To study hospital internal processes and effects of interprofessionality, we will look at compliance and agreement of the three health professions (physicians, nursing, and social workers) in the use of “In-HospiTOOL”, and delays from the anticipated to the effective discharge date as compared to discharge date anticipated by the different health care professionals on admission and during the course of the hospital stay. We will use the above-mentioned outcome data set as benchmark to establish a risk-adjusted resource and quality cockpit to compare different hospitals and demographics (corresponding to Module 3).

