### Rationale of the study and overall aim

The main reason for the large controversy of the different tool’s effectiveness in elderly, polymorbid patients is mainly explained by the current lack of evidence. Hence, a large prospective multicenter trial is warranted to investigate the effects of a patient in-hospital management tool (“In-HospiTOOL”). Using an interrupted time series (ITS) model to gather detailed treatment and outcome data of elderly, polymorbid medical patients during the in-hospital stay and 30 days after admission, we will investigate differences in resource use (Module 1), interprofessional collaborations (Module 2), and establish a representative benchmarking database to promote measurement and display of quality of care [14] across different sized Swiss hospitals (Module 3).

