### Data collection process

The study period is divided into three 6-month phases, whereas the observation and the intervention phase until the end of January 2019 are season-matched, interrupted by a run-in non-season-matched implementation phase. The period of “In-HospiTOOL” implementation in the participating hospitals will be devoted to technical implementation, training of involved study personnel, nurses, social workers, physicians, and pilot testing. We will collect data throughout all three study periods by using electronic medical records and will contact all patients 30 days after hospital admission by phone interview. Data from the structured phone interviews will be stored on a data base using the secuTrial© software (secuTrial®; interActive Systems GmbH, Berlin, Germany).

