### Theoretical aspects, hypothesis

#### Module 1 resource (mis-)utilization & allocation

We hypothesize that implementing the “In-HospiTOOL” in a nationwide multicenter setting will significantly shorten length of hospital stay without compromising patient outcomes and functional independence. Systematic early determination of clinical stability, estimation of the post-acute care referral probability (using the Post-acute care discharge [PACD] score [15]), fixing a possible discharge date after initial ED assessment as well as a tight interprofessional collaboration enabled through an electronical communication platform (“Visitentool”, Fig. 1) will result in decreased waiting times contributing to the shortening of length of hospital stay [16–18].

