#### User-oriented key data benchmarking

Based on the sounding board consensus, we designed a structured questionnaire (see Additional file 2) to perform phone interviews with all included patients 30 days after hospital admission to assess their outcome data and satisfaction. Each study site establishes a local interview team performing the 30-day structured follow-up interviews. Depending on the cumulative number of patients, between 3 and 7 part-time working persons were recruited by each study site, respectively, and were finally instructed by the core study nurse team.

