#### Interrupted time series (ITS) model

We will analyze the trends in length of hospital stay from start of observation through the end of the intervention period (18 months). For this purpose, we will conduct an ITS as a sensitivity analysis. We will implement the ITS using generalized estimating equations (GEE), to examine linear trends in weekly, hospital-level, risk-adjusted length of hospital stays. ITS models will be tested for autocorrelation to control for seasonal trends using the Durbin-Watson statistics [25]. We will analyze the change in trend between all three time periods. This approach allows us to distinguish between a possible effect of the intervention and a difference from underlying trends facing both study groups and can also help to analyse whether the intervention effects will sustain over time. We will calculate weekly-adjusted length of hospital stay using linear GEE that includes all lengths of hospital stay from the control and intervention populations and all above mentioned risk factors. We will graph weekly length of hospital stay for all populations over time and use the estimated weekly means for control and intervention patients to assess for a weekly difference between the two groups. Finally, we explore whether the adjusted weekly length of hospital stay decreases in the intervention period and whether there will be an independent time trend effect induced by the intervention only [26].

To summarize, we will use four statistically hypothesis tests during each period: (i) Are there significant trends in length of hospital stay change during the period. (ii) Will the trend differ between the control and intervention populations (the interaction between time and control or intervention conditions) during the period. (iii) Will the trend during the intervention period differ from the trend during the observation period within all three conditions. (iiii) Will the magnitude of the altered trend between the intervention and the observation period differ between the three conditions (the interaction between the change in slope and intervention or control conditions). These models will also be implemented for the analyses of the secondary endpoints.

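### Readmissions and unplanned GP/ED visits are counted to day 30 after admission, so a tool that shortens the stay lengthens time at risk and biases these comparisons against itself

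*Protocol article*

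**What the plan says.** All references are to the protocol article.

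- **Follow-up is anchored at admission throughout.** Data collection process: the study "will contact all patients 30 days after hospital admission by phone interview". User-oriented key data benchmarking: the questionnaire serves "to perform phone interviews with all included patients 30 days after hospital admission to assess their outcome data and satisfaction". Rationale of the study and overall aim: data are gathered "during the in-hospital stay and 30 days after admission".
- **One interview serves all endpoints.** Under Endpoints, patients are "contacted 30 days after admission by phone for a structured and blinded interview to assess primary and secondary endpoints". Unplanned readmissions and unplanned GP or ED visits are listed as secondary, with no window of their own.
- **The primary endpoint uses the same window.** It is "length of hospital stay within 30 days after admission including readmissions during this period". The index stay is verified from hospital data, "complemented by 30-day interviews regarding possible secondary hospitalizations".
- **The hypothesis has two parts.** Under Module 1, the tool "will significantly shorten length of hospital stay without compromising patient outcomes and functional independence".
- **The analysis has no exposure term.** The statistical section adjusts all endpoints for baseline characteristics and study centre. Of the difference-in-differences and time-series models it says: "These models will also be implemented for the analyses of the secondary endpoints". Neither discharge date nor days at risk is mentioned.

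**The concern.** A patient cannot be readmitted, or make an unplanned GP or ED visit from home, before leaving hospital. With observation closing 30 days after admission, each patient's time at risk is 30 days minus the index stay. The tool is designed to change that stay, so exposure time for these events depends on the primary outcome.

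If the tool shortens stays, patients in the intervention phase are observed for longer after discharge. Their observed proportion with an event then rises even if the daily risk after discharge is the same. Neither the baseline covariates nor the control hospitals remove this, because the intervention itself creates the difference in exposure.

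Readmission is one of the outcomes by which a reader would judge whether earlier discharge does harm. The bias runs against a tool that works and grows with its success. The Endpoints section also uses these outcomes to benchmark hospitals. A hospital with shorter stays would look somewhat worse on readmission for the same reason.

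**Working it through.** **Inputs from the article.** The window is 30 days from admission. Planned enrolment is about 35,000 over three phases, or 35,000 / 3 = 11,667 per phase if the phases are equal (an assumption).

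**Assumed inputs.** The article gives no mean stay, expected reduction, readmission risk or significance level. I took mean stays of 6 to 10 days, reductions of 0.5 to 2 days and a two-sided 5% level. Event risk is defined in each step. The article has no figure on this point to reproduce.

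**Step 1: one typical patient.** With index stay L, days at risk are 30 − L. For a constant hazard h after discharge, the observed risk is p = 1 − exp(−h(30 − L)).
- L = 8, p = 12%: h = −ln(0.88) / 22 = 0.00581 per day.
- L = 7, same h: days at risk rise from 22 to 23 (+4.5%), and p = 1 − exp(−0.00581 × 23) = 12.5%. The risk ratio is 1.04.
- With a front-loaded hazard (Weibull, shape 0.7), p becomes 12.35% and the ratio 1.03.

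**Step 2: a distribution of stays.** Stay is lognormal with mean 8.8 days and log-SD 0.6 to 0.9. The true 30-day post-discharge risk is 10% or 15% in both phases, with h = −ln(1 − risk) / 30. Every stay is cut by the same amount. The observed proportion is the mean of 1 − exp(−h × max(30 − L, 0)).

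| Days saved | Risk 10%: observed | Risk 15%: observed | Spurious risk ratio |
|---|---|---|---|
| 0.5 | 7.2–7.3% to 7.3–7.5% | 10.8–11.0% to 11.1–11.3% | 1.02 |
| 1 | 7.2–7.3% to 7.5–7.6% | 10.8–11.0% to 11.3–11.5% | 1.04–1.045 |
| 2 | 7.2–7.3% to 7.8–7.9% | 10.8–11.0% to 11.8–11.9% | 1.08–1.09 |

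A gamma-distributed stay (mean 8 days, shortened proportionally, observed risk about 12%) gives 1.021, 1.042 and 1.085. Over the full grid (stay 6 to 10 days, reduction 0.5 to 2 days, observed risk 8 to 18%, constant or front-loaded hazard) the ratio runs from 1.01 to 1.10. A window of fixed length from discharge gives exactly 1.000 in every case.

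**Step 3: when the tool also lowers the hazard.** In the gamma model with one day saved:

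| True fall in hazard | Ratio, admission window | Ratio, 30 days from discharge |
|---|---|---|
| 0% | 1.042 | 1.000 |
| 3% | 1.013 | 0.972 |
| 5% | 0.994 | 0.954 |
| 10% | 0.945 | 0.908 |

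Break-even is a fall of about 1 − 22/23 = 4.3%.

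**Step 4: size against sampling error.** For one day saved in Step 2, the standard error of a simple two-phase comparison is sqrt(2p(1 − p) / 11,667), about 0.34 points (10% risk) or 0.41 points (15% risk). Bias divided by standard error is 0.91 to 1.17. An unadjusted two-proportion test would then reject in about 15 to 22% of trials with no true change. If clustering and the control contrast inflate the variance 2 to 3 fold (an assumption), this falls to about 8 to 13%.

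**The case against.** The strongest reply is that the admission anchor is deliberate and sound. The tool cannot shift the date of admission, every patient is retained in line with the intention-to-treat principle, and readmission days already count in the primary endpoint. That stands for the primary endpoint and mortality, and it is a reason to keep the admission-based readmission proportion. It does not make exposure equal for events that can occur only after discharge.

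Second, the article is condensed. The readmission endpoint has no explicit window, effect measure or denominator. This also stands: day 30 after admission is inferred from the interview timing and the primary endpoint's wording. A reader might infer that patients still in hospital on day 30 are kept in the denominator, but the article does not say so. What it does fix is the only described patient contact, at day 30 after admission. It describes no later source for readmissions elsewhere or for GP visits.

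Third, a reader might infer that a successful tool will appear to increase readmissions. The article does not support that. The bundle includes a reengineered discharge with teach-back education, so an unchanged hazard is only one possibility, and Step 3 shows a 10% fall still appearing as a reduction. Nor may the 15 to 22% rejection rate be read as that of the planned analysis, which is a difference-in-differences model with a GEE time series.

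Fourth, readmission is one of several unranked secondary outcomes, and the bias does not hide harm from early discharge. Both are true, and they limit the severity. A bias of known direction still distorts the reading of this outcome.

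**Conclusion.** The point holds as a modest, directional bias in the secondary endpoint of unplanned readmissions and unplanned GP or ED visits. Under the assumptions in Step 2, the spurious risk ratio is about 1.02, 1.04 and 1.08 to 1.09 for 0.5, 1 and 2 days saved. It is smaller if risk is concentrated soon after discharge. It masks true reductions of up to about 4% per day saved and attenuates larger ones. It produces an apparent increase only when the hazard is unchanged or falls by less than the gain in days at risk. The size rests wholly on assumed stays and risks; the direction follows from the admission-based window and from the hypothesised shorter stay. The primary endpoint and 30-day mortality are not affected. The change is worth making because it is cheap and the outcome bears on the claim that patients are not harmed.

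**What to change.** 1. Keep the admission-based window for the primary endpoint and mortality, and keep the admission-based readmission proportion.
2. Add an analysis of unplanned readmission and of unplanned GP or ED visits from the discharge date, among patients discharged alive. Use time to event with death as a competing event, censored at day 30 after admission, and report cumulative incidence at a short fixed horizon such as day 14 after discharge. A rate with a days-at-risk offset is an alternative, but it assumes a roughly constant rate after discharge.
3. Where hospital records allow, add same-hospital readmission within 30 days of discharge.
4. Base the conclusion on readmission, as part of the claim that outcomes are not compromised, on both the admission-based and the discharge-based results.

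**Cost.** Analysis-plan wording, and event dates recorded at the interview or taken from records. No extra patient contact is needed.

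**Limits to state.** The added analysis conditions on live discharge, which the tool could influence. Patients with long stays are censored early: with a day-14 horizon, anyone staying beyond 16 days is incompletely observed (30 − 14 = 16), about 10 to 13% under the stay distributions in Step 2. They are plausibly sicker, so this censoring may be informative and may differ by phase. Adjust for the planned baseline covariates and report how many are affected in each phase.

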## Methods/design

### Aim and study design

The “In-HospiTOOL” study is a quasi-experimental investigator-initiated, multicenter effectiveness trial investigating the effects of a new patient in-hospital management tool to improve length of hospital stay and other outcomes using an ITS model. The overall 18-month study time is divided in a 6-month observational phase, a 6-month implementation phase, and a 6-month intervention phase.

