Our study has several potential limitations. First, inclusion of about 35`000 patients over the 18-month study time frame is ambitious. However, based on our large experience from previous multicenter studies, a well-established multicenter research network, and the high prevalence of hospitalized multimorbid patients eligible for this trial, we are convinced that the trial is feasible. The second limitation of this trial is the lack of randomization. Methodologically, in a trial whose intervention focuses on the process of care, neither patient-level randomization nor a randomized cross-over design was feasible as a carry-over effect would have biased the control group. For a cluster randomized trial, a large number of similar clusters (i.e. hospitals) would be needed – which is challenging in Switzerland particularly in light of the limited study budget. Therefore, we chose an ITS model in a quasi-experimental study design using administrative data from non-participating hospitals as a control group. Doing so, we account for differences in the patient population that may occur due to epidemiological variations. Third, as a pragmatic trial with a bundled intervention, it will be challenging to understand which part of our intervention shows clinical effects, leading to potential participation bias. Nonetheless, the large amount of health care data collected will also allow to provide scientific evidence as to which elements of patient management are influenced by the intervention.

In conclusion, this pragmatic comparative effectiveness health services research trial will inform whether the implementation of a novel electronic tool for inpatient management optimizes inter-professional collaboration and thereby reduces length of hospital stay without derogating subjective and objective patient-oriented measures. Our trial will help to compare between diverse transition processes within seven different hospitals and to create a benchmarking for inpatient care quality. This study synergizes national networks and, thus, has the potential to become a cornerstone in the present public healthcare discussion.

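### The 30-day interview is called blinded, but phase follows from the admission date and site-recruited teams make the calls, so blinding of interviewers to study phase cannot be ensured

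*Protocol article*

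**What the plan says.** The Endpoints section states that all patients are phoned at 30 days for a "structured and blinded interview", which is to serve both the primary and the secondary endpoints. The primary endpoint is the number of hospital days within 30 days of admission, readmissions included. The index stay is verified from hospital data and then "complemented by 30-day interviews regarding possible secondary hospitalizations". Satisfaction and functional status with quality of life (EQ-5D) are among the secondary endpoints.

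Exposure is defined by time alone. Under Aim and study design, the 18 months are "divided in a 6-month observational phase, a 6-month implementation phase, and a 6-month intervention phase". Data collection process adds that "the observation and the intervention phase until the end of January 2019 are season-matched". The limitations in the Discussion (Scientific significance) say: "The second limitation of this trial is the lack of randomization".

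On who makes the calls, User-oriented key data benchmarking says: "Each study site establishes a local interview team performing the 30-day structured follow-up interviews". These are 3 to 7 part-time persons recruited by each site and instructed by the core study nurse team. Controls come from Federal Statistical Office data on length of stay (Control population). The article does not say who is blinded, to what, or how.

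**The concern.** Blinding an outcome interview normally means that the interviewer does not know which condition the patient belongs to. Here the condition is the calendar phase, and the call is timed from the admission date, which determines that phase. The article describes no concurrent untreated group within the participating hospitals and no staggered start that would hide the phase.

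Readers who take the word at face value would credit interview-based outcomes with protection against assessor bias that the design does not provide. Two uses are at stake:

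- **Primary endpoint.** The interview supplies information on later hospital stays, which count as days in the endpoint.
- **Claim of no harm.** The trial aims to show a shorter stay without worse patient-oriented outcomes. Satisfaction and EQ-5D are part of that case, and they are more open to the manner of questioning than a record of a hospital stay.

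The limitations listed in the Discussion do not mention assessor or reporting bias.

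**Working it through.** The plan gives no figure on this point, so there is none to reproduce.

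**1. Does the date reveal the phase?**

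Inputs from the article: three consecutive six-month phases, the last ending in January 2019, and a call 30 days after admission. Assumptions: phases run by whole calendar months, with the same dates at all sites.

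| Phase | Derived dates | Days |
|---|---|---|
| Observation | 1 Aug 2017 to 31 Jan 2018 | 184 |
| Implementation | 1 Feb to 31 Jul 2018 | 181 |
| Intervention | 1 Aug 2018 to 31 Jan 2019 | 184 |

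Total: 184 + 181 + 184 = 549 admission dates. With calls at exactly +30 days there are 549 interview dates, and 0 fit more than one phase.

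If calls may fall within ±w days (an assumption; the article gives no window), there are 549 + 2w possible interview dates. Of these, 2w are ambiguous at each of the two phase boundaries, so 4w in all:

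- w = 7: 28 of 563, or 5.0%
- w = 14: 56 of 577, or 9.7%

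The admission date, which is needed to time the call, removes even this ambiguity.

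**2. Which endpoints depend on the interview?**

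- Index stay: hospital data; not affected.
- In-hospital mortality: known without a call; not affected.
- Later hospital days within 30 days: complemented by the interview; exposed.
- Satisfaction and EQ-5D: patient-reported at 30 days; exposed.

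**3. Would the control group remove a reporting effect?**

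Let b be the mean error in days per patient that the interview introduces at the participating hospitals in a given phase. No interview is described for the controls, so they carry no such term. Then

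difference in differences = true effect + (b in the intervention phase − b in the observation phase).

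An error that is the same in both phases cancels. An error that changes with phase stays in full, because nothing in the control series offsets it.

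**4. How large could it be?**

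If the share of rehospitalisation days elicited changes by a fraction d between phases, the shift is about

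readmission proportion × days per readmitted patient × d.

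The article gives none of the three. Purely as an illustration with assumed inputs, take 10% readmitted, 5 days each, and d of 5% to 20%. Then 0.10 × 5 = 0.5 day per patient, and 0.5 × 0.05 to 0.5 × 0.20 gives 0.025 to 0.10 day, in either direction.

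For scale, take an assumed SD of 6 days and 35,000 / 3 ≈ 11,667 patients per phase. The standard error of a simple two-phase comparison is 6 × √(2 / 11,667) = 0.079 day. This treats patients as independent within seven hospitals and leaves out the control contrast, so it is probably too small and makes the shift look relatively larger.

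**The case against.** A fair defence runs as follows. The article does not say that interviewers know the phase dates, the hypothesis or whether a given patient was managed with the tool. Phase is not the same as individual tool use: compliance is monitored, and missing tool forms are foreseen. Interviewers could be masked to tool use, to the records or to the hypothesis, and a condensed article may leave such procedures to the full protocol. The questionnaire is structured, and whether a patient was rehospitalised is a factual item. Electronic medical records are used in all three phases.

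Much of this stands, and it rules out several stronger readings that a reader might infer:

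- *Outcomes are collected unblinded, or no interviewer can be blinded.* This is an inference. The document supports only that blinding to phase cannot be ensured.
- *Interviewers are treating staff or tool users.* They are described only as part-time persons recruited by the site, and the staff groups listed under Coaching do not include them.
- *Patients know that they received a new discharge process.* The article does not say so, and it does not claim that patients are blinded.
- *About 35,000 interviews are affected.* That figure is planned enrolment; some patients will die, and missing interviews are foreseen.
- *The bias favours the tool.* No direction follows from the text.

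The defence does not rescue the word itself. The article asserts blinding without qualification for an interview that assesses the primary endpoint, in a design where the date discloses the condition. That is a statement which does not fit the design, and not merely an omitted detail.

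**Conclusion.** The concern holds in limited form. The article claims a blinded interview, while its own description of phases, call timing and interview teams means that blinding to study phase cannot be ensured. The calendar result rests on phase dates common to all sites, which is how the article presents them.

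The exposed part of the primary endpoint is limited to rehospitalisation days that reach the data through the interview. An error there biases the comparison only if it differs between phases. Whether it does, by how much and in which direction cannot be computed from the document. The illustrative range of 0.025 to 0.10 day shows an order of magnitude under chosen inputs and is not an estimate. Correction is still worthwhile, because the statement touches the primary endpoint and part of the no-harm argument, and it is cheap to put right.

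**What to change.** 1. In Endpoints, replace the blinding claim with a statement that interviewers are not blinded to study phase. If they are masked to something else, such as the hypothesis or individual tool use, say to what and how.
2. Take readmissions and rehospitalisation days from hospital or administrative records in all three phases wherever available. Keep the interview to capture stays outside those records. Reducing it to a mere cross-check could lose such stays.
3. Add a sensitivity analysis of the primary endpoint that uses record-based days only.
4. List the lack of blinding to phase as a limitation for satisfaction and EQ-5D.

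Cost: a change of wording, record queries and a little more analysis. The main downside is that records may miss stays outside the study hospitals, so the record-only analysis may undercount days and should be read beside the combined one.
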